### Exposure

CGM glucose is the exposure of interest (summary statistical measures, mean FDA glucose and glucotype).

### Primary outcome

The primary maternal outcome is a clinical diagnosis of GDM, and the primary neonatal outcome is Large for Gestational Age (LGA) at birth (> 90th centile defined by customised birthweight centile).

### Secondary outcomes

Secondary outcomes include other measures of fetal growth (to include: birthweight; SGA on GROW centile; LGA and SGA defined on Intergrowth and WHO centiles; neonatal adiposity at birth; USS measures of abdominal circumference, estimated fetal weight at 28, 32 and 36 weeks gestation) and the range of maternal and neonatal outcomes as above.

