To mitigate against hyperglycemia related fetal growth and associated adverse pregnancy outcome, clinical guidelines currently recommend testing for pregnancy related dysglycemia at 24–28 weeks gestation by an oral glucose tolerance test (OGTT) [10]. NICE recommends diagnosis of GDM on the basis of a raised fasting or 2 h glucose. This late pregnancy diagnosis of GDM is an increasing cause for concern; we have shown that excess fetal growth assessed by ultrasound scan is detectable from 20 weeks’ gestation, pre-dating biochemical diagnosis of GDM [11, 12]. Whilst we now know that testing at 24–28 weeks gestation is too late to prevent abnormal fetal growth, there is no validated test for earlier diagnosis and the optimal time of screening and treatment for dysglycemia remains unknown [13]. Indeed, despite OGTT testing, the majority of LGA babies are born to mothers without a diagnosis of GDM [8, 14, 15]. This concurs with the recognition that the OGTT is insufficiently sensitive and that many women who could benefit from treatment will not be correctly identified, contributing to the failure to improve outcomes. The OGTT, recognised to be an outdated test for diabetes diagnosis, is now used only in pregnancy. It is known to be poorly reproducible: 40% of pregnant women who had a 2nd OGTT immediately after an abnormal OGTT had normal results and vice-versa [16].

Glucose control is dynamic, with glucose tolerance and insulin sensitivity varying across the 24 h day with a circadian rhythm [17, 18]. Insulin sensitivity also varies across pregnancy, with insulin resistance increasing with gestation [19]. As the OGTT relies on just two glucose readings taken two hours apart on one day, it cannot detect the nuances of daily glycemic variations, or changes across pregnancy.

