##### Assessment of fetal growth

Infant birthweight will be recorded. LGA will be defined as birthweight > 90th centile and SGA < 10th centile, using customised GROW birthweight centiles, ([contact]) which adjusts for maternal height, weight, ethnicity, parity, neonatal sex and gestational age. Fetal anthopometry measures, including sum of skin folds and neonatal fat mass, will be taken after delivery. USS are performed routinely in all pregnant women at 12 weeks (dating scan) and 20 weeks (anatomy scan) gestation and in women diagnosed with GDM growth scans are performed at 28, 32 and 36 weeks gestation [10]. Fetal biometry and estimated fetal weight will be obtained from each.

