### Statistical analysis plan

A Directed Acyclic Graph will be developed to direct the modelling of the data to correctly identify confounders, mediators and competing exposures [34].

Detailed CGM glucose summary statistics, functional data analysis profiles and glucotype will be generated for both weeks of each of the five measurement periods (a minimum of 96 h CGM data at each visit will be needed to be included in the analysis). Means ± SD values or percentiles appropriate to the variable under consideration will be reported for the covariates in relation to the outcome. Primary analysis will initially retain the measures of glucose (as the primary exposure of interest) distinct at different time of gestation. The modelling will adjust for week of gestation, and is already adjusted for maternal height, weight, ethnicity, parity, neonatal sex using the GROW centile. Selected CGM outcomes will also be calculated to compare the between group differences. For assessing group differences in secondary outcomes of fetal growth measures and maternal and neonatal outcomes, regression models will be used to compare continuous and ordinal variables, logistic regression will be used to compare categorical variables, and Poisson regression models will be used to compare event rates. Missing data for outcomes will not be imputed. Available case analysis method will be used for secondary outcome analyses in each time point.

Functional Data Analysis: The life course nature of the data means that, for any individual, the measures will be more correlated than those measures between individuals. A functional multilevel model will be used to reflect the complex structure of the data, as well as covariance and correlations therein, to correctly infer statistical relevance within the model. Point estimates, 95% confidence intervals and p-values will be reported for the average effect at each time point of CGM measurement. Residual values will be examined for an approximate normal distribution. If values are highly skewed then a transformation or robust statistical methods will be used instead.

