#### Sample size estimation

The sample size calculations are based on two of the key findings from our pilot data: (1) mean CGM glucose; (2) glucotype. For the first a sample size of 280 women, will give 28 women who have LGA and 252 who do not, with a 90% power to detect a difference in glucose of 0.4 mmol/l with a SD of 0.6 at p = 0.05. This is a clinically relevant effect size in pregnancy. This has been illustrated in HAPO [8] with an OR 1.38 (1.32–1.44) for birthweight > 90th centile, with an increase in glucose of 0.4 mmol/l; A similar effect size was seen in CONCEPTT [26] and previous CGM analysis in pre-gestational diabetes [24, 29, 30]. Furthermore, improving CGM glucose by this small, but clinically relevant, amount in pregnancy is significantly associated with improved clinical outcomes, including LGA [26]. To ascertain the exposure of severe glucotype to LGA a sample size of 384 women, will give 38 women with LGA, and 346 who do not, with 90% power to detect a difference in glucotype (based on the prevalence of severe glucotype in the non LGA group of 37%, and in the LGA group of 64%). As GDM diagnosed by OGTT has a prevalence of 10%, then the sample sizes for this outcome, with these two exposures, are the same as for LGA. Allowing for ~ 30% drop out (including miscarriage and/or incomplete data capture) 500 recruits will be needed.

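### Abdominal circumference and estimated fetal weight at 28, 32 and 36 weeks are listed without restriction, but scans at those weeks are scheduled only for women with GDM, so the available-case analysis is mainly of a GDM-selected group

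*Protocol article*

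**What the plan says.** Under *Secondary outcomes*, the protocol article lists "USS measures of abdominal circumference, estimated fetal weight at 28, 32 and 36 weeks gestation" alongside birthweight, alternative size-for-gestation definitions and neonatal adiposity. No subgroup is attached to any of them.

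Under *Assessment of fetal growth*, it describes where the ultrasound data come from. For the whole cohort: "USS are performed routinely in all pregnant women at 12 weeks (dating scan) and 20 weeks (anatomy scan) gestation". For later pregnancy: "in women diagnosed with GDM growth scans are performed at 28, 32 and 36 weeks gestation". Biometry and estimated fetal weight are taken from these scans. *Study visits and data collection* adds only that scan details are recorded, and Table 1 has no ultrasound row.

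Under *Statistical analysis plan*, missing outcomes are not imputed, and "Available case analysis method will be used for secondary outcome analyses in each time point". Under *Primary outcome*, the primary maternal outcome is a clinical diagnosis of GDM.

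**The concern.** The three gestations in the outcome list are exactly those at which the article schedules scans for women with GDM and for no one else. Applied as written, the available-case rule would analyse whoever happens to have a late scan, and on the stated schedule that means mainly women already diagnosed with GDM.

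This differs from incidental missing data in three ways:

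- The set is selected on the study's primary maternal outcome, which the study expects CGM glucose to predict. For CGM recorded before diagnosis, this is selection on something downstream of the exposure.
- The selected women are under GDM care, which may itself alter late growth.
- Any comparison of late scan measures between women with and without GDM has no scheduled comparison group.

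The relation of CGM measures to fetal growth is one of the primary research questions, and the *Background* says that "the majority of LGA babies are born to mothers without a diagnosis of GDM". Those pregnancies have no scheduled scan after 20 weeks. A late-scan result presented as a general fetal-growth finding would describe mainly the diagnosed minority.

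**Working it through.** **Inputs, all from *Sample size estimation*:** 500 recruits; dropout of about 30%, which includes miscarriage and incomplete data capture; GDM prevalence 10%; evaluable sample 384.

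**The plan's own figures.** The article gives no number for women with late scans, so its sample size is the nearest figure to check.

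- Comparing severe glucotype of 64% with 37% in groups of 38 and 346 (two-sided 0.05) gives power 0.902, which agrees with the stated 90%.
- 384 x 1.3 = 499, which rounds to the stated 500.
- Taking 30% off 500 leaves 500 x 0.70 = 350. That is below 384, which is a separate matter.

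**Women with a scheduled late scan = women remaining x GDM prevalence**

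| Basis | Calculation | Women |
|---|---|---|
| 500 recruits, 30% dropout | 500 x 0.70 x 0.10 | 35 |
| Stated evaluable sample | 384 x 0.10 | 38 |
| 500 recruits, no dropout | 500 x 0.10 | 50 |

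On the first basis, 350 - 35 = 315 women (90%) have no scheduled scan at these weeks. If prevalence were 5% to 20% (an assumption), 350 women would give about 18 to 70. The OGTT is at 24–28 weeks (*Other glucose measures*), so some diagnoses may come too late for the 28-week scan, and the count there could be lower.

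**Precision.** By Fisher's z, the smallest correlation detectable with 80% power at two-sided 0.05 is tanh[(1.96 + 0.84)/sqrt(n - 3)]. Power at a true correlation of 0.25 is Phi[atanh(0.25) x sqrt(n - 3) - 1.96].

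| n | Detectable correlation | Power at 0.25 |
|---|---|---|
| 35 | tanh(2.80/sqrt(32)) = 0.46 | 30% |
| 50 | tanh(2.80/sqrt(47)) = 0.39 | 42% |
| 350 | tanh(2.80/sqrt(347)) = 0.15 | 99.7% |

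**Selection, as illustration only.** None of these inputs is in the documents.

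- *Range restriction.* Treat GDM as the top 10% of a normally distributed liability that correlates 0.5 to 0.7 with CGM glucose. In simulation, the SD of glucose among the selected women falls to 0.89 to 0.77 of its cohort value. A cohort glucose–growth correlation of 0.30 then falls to about 0.27 to 0.24.
- *Loss of the path through liability.* Let growth = b x glucose + c x liability + error, with glucose and liability correlated 0.3 to 0.5 and c of 0.1 to 0.3. With b = 0.2, the glucose slope in the top 10% is 10–34% smaller than in the cohort. With b = 0.4 the loss is about 6–21%, and with b = 0.1 about 19–47%. With c = 0 it is essentially nil.

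The direction is consistent, but the size depends almost wholly on the assumed values.

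**The case against.** The two sections can be read together. The outcome list never says it covers the whole cohort, its gestations match the GDM schedule, and the source of the scans is disclosed. On that reading the fault is an omitted label. Also, this is a condensed article, and analysis sets per outcome are often left to a fuller plan. This has some force, but the article does fix a rule for secondary outcomes, available cases at each time point, and following that rule produces the selected set. The planned causal diagram can guide adjustment; it cannot supply scans that were not done.

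Several stronger readings are tempting, and the documents do not support them:

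- *Exactly 35 women will have data and 90% will have none.* The article describes scheduled care and does not say that no one else is scanned. Women without GDM may have clinically indicated scans, in unknown number. Dropout includes incomplete data capture, which need not mean missing scans, so 50 is possible at 10% prevalence.
- *The association will be attenuated by a stated percentage.* Every such figure rests on assumed effects, and in the slope model the direct effect of glucose is not distorted.
- *GDM is a consequence of the exposure throughout.* This fits mainly CGM before diagnosis. The 26–28 week recording overlaps the OGTT window, and the 34–36 week recording follows it.
- *Fetal growth in women without GDM is not studied.* Birthweight, LGA, SGA and neonatal adiposity are planned without restriction to GDM, and the 20-week scan covers all women.

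**Conclusion.** The point holds for two secondary measures, abdominal circumference and estimated fetal weight at 28, 32 and 36 weeks. They are listed without restriction, scheduled only in women with GDM, and subject to an available-case rule. The analysed set would be mainly GDM-selected and under GDM care: about 35–50 women at the plan's own prevalence, plus unscheduled clinical scans in others. Only correlations of roughly 0.4 to 0.5 would be detectable with 80% power.

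The count rests on the 10% prevalence and on dropout between none and 30%. Attenuation by selection is plausible in direction, and its size is undetermined. Clinically indicated scans in women without GDM would add numbers but would themselves be a selected group. The primary outcomes, the sample size and the growth measures at birth are unaffected. The point should be settled before analysis; it does not threaten the study as a whole.

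**What to change.** Reconcile *Assessment of fetal growth* with *Secondary outcomes* by stating who contributes scans at 28, 32 and 36 weeks. If the schedule stands as written:

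- label these outcomes as a GDM-subgroup result in the outcome list;
- take them out of the cohort-wide available-case analyses in *Statistical analysis plan*;
- report them descriptively within the GDM group, with the number scanned at each gestation, keeping CGM before and after diagnosis separate;
- show any clinically indicated scans in women without GDM separately, not pooled;
- base cohort-wide conclusions on late growth on the birth measures already planned for every baby.

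If late scan data are in fact to come from the whole cohort, the article should say how they are obtained.

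For the schedule as stated, the cost is wording only, with no extra data collection. The downside is a narrower fetal-growth claim for these two measures.

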### Statistical analysis plan

A Directed Acyclic Graph will be developed to direct the modelling of the data to correctly identify confounders, mediators and competing exposures [34].

Detailed CGM glucose summary statistics, functional data analysis profiles and glucotype will be generated for both weeks of each of the five measurement periods (a minimum of 96 h CGM data at each visit will be needed to be included in the analysis). Means ± SD values or percentiles appropriate to the variable under consideration will be reported for the covariates in relation to the outcome. Primary analysis will initially retain the measures of glucose (as the primary exposure of interest) distinct at different time of gestation. The modelling will adjust for week of gestation, and is already adjusted for maternal height, weight, ethnicity, parity, neonatal sex using the GROW centile. Selected CGM outcomes will also be calculated to compare the between group differences. For assessing group differences in secondary outcomes of fetal growth measures and maternal and neonatal outcomes, regression models will be used to compare continuous and ordinal variables, logistic regression will be used to compare categorical variables, and Poisson regression models will be used to compare event rates. Missing data for outcomes will not be imputed. Available case analysis method will be used for secondary outcome analyses in each time point.

Functional Data Analysis: The life course nature of the data means that, for any individual, the measures will be more correlated than those measures between individuals. A functional multilevel model will be used to reflect the complex structure of the data, as well as covariance and correlations therein, to correctly infer statistical relevance within the model. Point estimates, 95% confidence intervals and p-values will be reported for the average effect at each time point of CGM measurement. Residual values will be examined for an approximate normal distribution. If values are highly skewed then a transformation or robust statistical methods will be used instead.

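### The GROW centile adjusts the outcome only, so the plan is wrong to count it as adjusting the glucose–LGA model; the estimate may be biased, in a direction the article does not settle

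*Protocol article*

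**What the plan says.** The article defines the exposure as follows: "CGM glucose is the exposure of interest (summary statistical measures, mean FDA glucose and glucotype". On outcomes, "the primary neonatal outcome is Large for Gestational Age (LGA) at birth", with LGA taken from the customised birthweight centile (Primary outcome section).

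The section Assessment of fetal growth describes the GROW centile as one "which adjusts for maternal height, weight, ethnicity, parity, neonatal sex and gestational age". The adjustment it describes is therefore of birthweight.

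The Statistical analysis plan section opens with the covariate strategy: "A Directed Acyclic Graph will be developed to direct the modelling of the data to correctly identify confounders, mediators and competing exposures". It then says that gestational week will be a model adjustment and that the modelling "is already adjusted for maternal height, weight, ethnicity, parity, neonatal sex using the GROW centile". Week of gestation is the only adjustment that this sentence places in the model itself. The other five characteristics are counted as dealt with because the outcome is customised. Nowhere is glucose said to be conditioned on them.

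**The concern.** Customising an outcome and adjusting a model are different operations. A covariate in a regression takes its influence out of both outcome and exposure. A customised centile takes a fixed amount out of the outcome, using coefficients that come from the centile, and leaves the exposure as it was. If CGM glucose varies with maternal weight, ethnicity or the other GROW factors, the customised outcome is being regressed on a glucose value that still contains them.

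A relation of this kind should not be presumed absent here, since BMI and ethnicity are two of the routes into the cohort (Eligibility criteria). What is at stake is the association for the primary neonatal outcome, and SGA on the same centile among the secondary outcomes. An analyst whose DAG shows maternal weight to be a confounder would read in the same section that weight has already been handled.

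**Working it through.** **The plan's own figures.** The article gives no figure for this bias. Its sample-size inputs for mean glucose are 28 women with LGA against 252 without, "with a 90% power to detect a difference in glucose of 0.4 mmol/l with a SD of 0.6 at p = 0.05". Taking a two-sided test, z = 0.4 / (0.6 × √(1/28 + 1/252)) = 0.4 / 0.1195 = 3.35, and power = Φ(3.35 − 1.96) = 91.7%. For glucotype, 38 against 346 with prevalences of 64% and 37% gives 90.2%. Both stated sizes are reproduced.

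**Algebra.** Let Y be birthweight, X glucose and Z the GROW factors (written as one score), with Y = bX + gZ + e and X = dZ + u.

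1. The centile removes kZ, leaving Y − kZ = bX + (g − k)Z + e.
2. Regressing this on X alone gives the slope b + (g − k) · d · var(Z)/var(X).
3. Regressing it on X and Z gives b, whatever k is.

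The slope in step 2 equals b only if d = 0 (glucose unrelated to the factors) or k = g (the centile carries direct effects only). With R² = d² · var(Z)/var(X), the cases are:

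- **Full effect,** k = g + bd: the slope is b(1 − R²), towards the null.
- **Direct effect,** k = g: no bias.
- **Under-correction,** k < g, with Z raising both glucose and birthweight: the slope exceeds b, away from the null.
- **Under-correction with opposite signs** (Z raises glucose but lowers birthweight): towards the null.

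**Simulation.** R² and k are not in the article, so both are assumed. Settings were 1,000,000 records, X and Z standardised, b = 0.20, g = 0.35 (−0.35 for opposite signs), residual SD 1, and LGA as the top 10% of the customised outcome. Under-correction means k = g/2. The first two result columns are for the full-effect case and the next two for under-correction with the same sign. Log-ORs come from logistic models without / with Z.

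| R² | Full effect: slope ÷ b | log-OR | Under-corrected: slope ÷ b | log-OR |
|---|---|---|---|---|
| 0.05 | 0.95 | 0.371 / 0.390 | 1.20 | 0.454 / 0.384 |
| 0.10 | 0.90 | 0.344 / 0.382 | 1.28 | 0.483 / 0.380 |
| 0.20 | 0.80 | 0.313 / 0.389 | 1.40 | 0.533 / 0.390 |
| 0.30 | 0.71 | 0.274 / 0.390 | 1.48 | 0.569 / 0.389 |

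With direct-effect coefficients the ratio was 0.99 to 1.00 throughout. With opposite signs and under-correction it was 0.80, 0.72 and 0.60 at R² = 0.05, 0.10 and 0.20. With Z in the model, the log-OR stayed at about 0.38 to 0.39 in every scenario.

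**Power, full-effect case only.** Multiplying the planned 0.4 mmol/l by 1 − R² gives 0.38, 0.36, 0.32 and 0.28. Power at N = 280 is then 89%, 85%, 76% and 65%, against 91.7% with no shrinkage. This is an illustration, not a forecast for this study.

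**The case against.** A reader might infer that the primary association will be shrunk towards the null and that the study loses power. The documents do not support that. Shrinkage by 1 − R² needs centile coefficients that match the full covariate–birthweight association in this cohort. The article gives neither the coefficients nor their source population, and other values give no bias or inflation. This objection stands, and it limits the claim to possible bias of unknown sign.

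The power figures are weaker still. The planned 0.4 mmol/l is a crude contrast between women with and without LGA, taken from pilot data. If the pilot used the same customised definition, any shrinkage is already inside the 0.4 and applying it again counts it twice. On that reading 35 against 315 women (70% of 500, with 10% LGA) gives z = 0.667 / 0.178 = 3.74 and about 96% power, whatever R² is. This stands too.

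A reader might also infer that the five factors will be left out. The article never says so: the DAG sentence allows further covariates, and a final covariate list commonly sits in an analysis plan that is not shown. This stands only in part. The point is not a missing list but a positive statement that is wrong, and it undercuts the DAG commitment made just before it.

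Last, the article also asks whether CGM can detect LGA better than the OGTT (Discussion). For that question the association of glucose with customised LGA, without covariates, is a legitimate target. This stands, so the correction belongs to the association analysis.

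**Conclusion.** The statement that the model is already adjusted through the GROW centile is wrong for GROW-defined LGA and SGA. Outcome-only customisation matches covariate adjustment only under one of two conditions: glucose unrelated to the factors, or a centile that carries glucose-free direct effects. The article establishes neither.

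The consequence is a possible bias in the glucose–LGA estimate whose direction and size cannot be fixed from the document. The computed range, about 60% to 148% of the adjusted slope, rests on assumed R², assumed coefficients and a single linear score for the factors; it shows what could happen, not what will. The conclusion does not depend on direction: in the linear case, entering the factors returns the adjusted slope whatever coefficients the centile uses, and the logistic simulation behaved the same way.

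The point is worth correcting before analysis because it touches a primary outcome. It does not show that the sample size is inadequate.

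**What to change.** In the Statistical analysis plan section, remove the clause that presents GROW as a substitute for adjusting the model, then state:

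- GROW continues to define LGA and SGA.
- For the association analysis, those of maternal height, weight at the first visit, ethnicity, parity and neonatal sex that the DAG identifies as confounders or competing exposures enter the LGA and SGA models as covariates.
- The model without them is reported alongside, and can serve the detection question.

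The cost is wording. Height, weight, ethnicity and parity are recorded at the first visit, and GROW already needs neonatal sex. The statistical price is model size. If all five factors enter, there are four terms for height, weight, parity and sex, two or three ethnicity contrasts, glucose and week of gestation, so 8–9 parameters on 35–38 LGA events. That is about four to five events per parameter (35/9 = 3.9; 38/8 = 4.8). A penalised fit such as Firth's, or collapsed ethnicity categories, should therefore be specified in advance.

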#### Study visits and data collection

Those who consent to take part will wear CGM for a fortnight on five occasions at ~ 10–12, 18–20, 26–28, 34–36 weeks gestation and immediately postnatally (to coincide with routine clinic attendance to minimise burden and to maximise participation/concordance where possible), see Table 1.

**Table 1 Tab1:** Spirit table

Summary of information collected		Visit 1	Visit 2	Visit 3	Visit 4	Visit 5
**Gestation (weeks)**		10–12	18–20	26–28	34–36	Immediate postnatal
**Enrollment**	Eigibility screen	x				
	**Consent**	x				
**Maternal**	Demographics	x				
	BMI	x	x	x	x	x
	BP	x	x	x	x	x
	Pregnancy outcome and complications					x
**Laboratory**	OGTT			x		
	HbA1c	x	x	x	x	x
	Blood stored	x	x	x	x	x
	Rectal swab			x		
	Placenta and cord blood stored					x
**CGM (2 weeks)**		x	x	x	x	x
**Neonatal**	Birthweight					x
	Anthropometry					x

Routinely collected anthropometric and sociodemographic information will be recorded at each visit including: weight, height, blood pressure, current medication. Age, parity, ethnicity, smoking will be recorded at the first visit. Blood samples will be taken at each visit for HbA1c and a sample stored (for subsequent analysis to identify mechanisms underlying dysglycemia, as well as predictors of GDM and fetal growth). The research midwife will insert the CGM sensor and the participant will return it via stamped addressed envelope for data download. Details on fetal growth from ultrasound scans (USS) and the OGTT results will be recorded. A rectal swab will be requested (optional) at 26–28 weeks gestation and stored for microbiome analysis.

Post-delivery, placenta and cord blood samples will be collected and stored in designated Human Tissue Act approved and compliant facilities for later analysis. Infant anthropometry measures will be taken (skin fold thickness). Maternal and neonatal outcomes will be collected as detailed below.

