##### Maternal and neonatal pregnancy outcomes

The following outcomes will be recorded: Maternal - hypertensive disorders (chronic; gestational; pre-eclampsia); mode of delivery inc. caesarean section; maternal weight gain; maternal length of stay; Neonatal - pregnancy loss < 20 weeks; stillbirth; termination; congenital anomaly; preterm births (< 37 weeks; <34 weeks) gestational age at delivery; neonatal hypoglycaemia, neonatal ICU admission, birth injury, shoulder dystocia, hyperbilirubinemia, respiratory distress; infant length of stay; composite neonatal outcome.

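### Secondary outcomes are not tied to CGM that precedes them: late visits cannot contain some of the events, and a Visit 4 profile can include glucose from after delivery

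*Protocol article*

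**What the plan says.** All places are in the protocol article.

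- **Study visits and data collection:** participants "will wear CGM for a fortnight on five occasions at ~ 10–12, 18–20, 26–28, 34–36 weeks gestation and immediately postnatally". Table 1 records pregnancy outcome and complications once, at Visit 5.
- **Exposure:** "CGM glucose is the exposure of interest".
- **Maternal and neonatal pregnancy outcomes:** the list includes pregnancy loss before 20 weeks, "preterm births (< 37 weeks; <34 weeks) gestational age at delivery", and "hypertensive disorders (chronic; gestational; pre-eclampsia". The section on secondary outcomes takes in this whole list.
- **Statistical analysis plan, profiles:** summary statistics, functional profiles and glucotype are generated for both weeks of each of the five periods, and "a minimum of 96 h CGM data at each visit will be needed to be included in the analysis".
- **Statistical analysis plan, models:** "Primary analysis will initially retain the measures of glucose (as the primary exposure of interest) distinct at different time of gestation". Missing outcomes are not imputed, and "Available case analysis method will be used for secondary outcome analyses in each time point". The functional data paragraph reports effects at each CGM time point.
- **Sample size estimation:** miscarriage is counted within the roughly 30% drop-out.

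No section says which CGM visits may be related to which outcome, or what happens to a trace when delivery falls within the fortnight of wear.

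**The concern.** CGM is the exposure, so it should be measured before the outcome it is meant to explain. Several listed outcomes are defined by when the pregnancy ends, and the CGM periods are spread across the same weeks. A woman contributes to a visit only if she is still pregnant when the sensor is fitted. For these outcomes, having late CGM therefore depends on not yet having had the event.

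Three things are at stake.

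- Some outcome-by-visit models have no possible events. Others keep a share of events that depends on the day the sensor was fitted.
- Comparing visits to see which window matters would mix the effect of glucose with survival to the visit.
- A late-pregnancy profile that runs past delivery is partly a postnatal profile. This happens more often in women who deliver early, so the measurement of the exposure depends on the outcome.

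**Working it through.** **The plan's own figures.** The article gives no event count or rate for pregnancy loss or preterm birth, so there is no figure on this point to reproduce. Its power statements concern the primary outcomes, and they reproduce (two-sided 0.05, normal approximation):

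- Mean glucose, 28 v 252: 0.4 / (0.6 × √(1/28 + 1/252)) = 3.35; 3.35 − 1.96 = 1.39; power 0.917.
- Glucotype, 38 v 346, 64% v 37%: (0.27 − 1.96 × 0.0836) / 0.0821 = 1.29; power 0.902.

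The point does not rest on these.

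**Inputs.** Fitting at 10–12, 18–20, 26–28 or 34–36 weeks; 14 days of wear; at least 96 h = 4 days of data.

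**Days in which a woman can be a case.** For an outcome with upper limit L, and 96 h of CGM required before the event:

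days at risk = L − (fitting date + 4 days), or zero if negative.

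| Outcome | Visit and fitting date | Days at risk |
|---|---|---|
| Loss <20 weeks | Visit 2 at 18+0 | 14 − 4 = 10 |
| | Visit 2 at 19+0 | 7 − 4 = 3 |
| | Visit 2 from 19+3 | 0 |
| | Visits 3 and 4 | 0 |
| Birth <34 weeks | Visit 4, any date from 34+0 | 0 |
| Birth <37 weeks | Visit 4 at 34+0 | 21 − 4 = 17 |
| | Visit 4 at 36+0 | 7 − 4 = 3 |
| | Visit 4 from 36+3 | 0 |

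Visit 5 CGM follows every one of these events.

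**Share of events kept or lost.** The article gives no timing of events, so these figures rest on assumptions.

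- *Visit 1, loss <20 weeks,* uniform from fitting to 20 weeks: (20 − 10.57)/10 = 94% kept if fitted at 10 weeks; (20 − 12.57)/8 = 93% at 12 weeks.
- *Visit 2, loss <20 weeks,* uniform over 10–20 weeks: (20 − 18.57)/10 = 14% kept if fitted at 18 weeks, and 0 at 20 weeks.
- *Visit 3, birth <34 weeks,* over 24–34 weeks. Uniform: (34 − 26.57)/10 = 74% kept if fitted at 26 weeks, 54% at 28 weeks. Linearly rising: 1 − (2.57/10)² = 93% and 1 − (4.57/10)² = 79%.
- *Visit 4, birth <37 weeks,* taking 30% of these births as before 34 weeks: share lost = 1 − 0.70 × k, where k is the share of 34–37 week births that fall after the 96 h. Fitted at 34 weeks, k = 0.81 (uniform) or 0.96 (rising), so 43% or 33% are lost. Fitted at 36 weeks, k = 0.14 or 0.27, so 90% or 81% are lost.

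**Wear beyond delivery.** 36+0 plus 14 days = 38+0, so 7 of 14 days follow 37+0. Even a fitting at 36+6 leaves 1 day before 37+0, so the most is 13 of 14. With both weeks profiled and no cut, a woman who delivers during wear and keeps the sensor on contributes postnatal readings. As written, those readings could also help her reach 96 h.

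**The case against.** **The time point may not be the CGM visit.** The available-case sentence does not name it, and it follows the sentence on missing outcomes. It could mean the growth scans at 28, 32 and 36 weeks. The sentence keeping glucose distinct by gestation is about the primary analysis, and the CGM time-point sentence sits in the functional data paragraph. This stands as a real ambiguity. Against it, pregnancy outcomes are recorded only once, so for them the natural repeated time point is the CGM visit. The trace problem does not depend on the reading.

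**This is detail for the analysis plan.** Pairing outcomes with windows is often left to it, and a Directed Acyclic Graph is promised to direct the modelling. That would answer a mere omission. Here the article states two rules, both weeks of every period and available cases in each time point, which give these results if followed as written.

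**Stronger readings that the documents do not support.**

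- A reader might infer that all CGM analyses of these outcomes fail. They do not: Visit 1 precedes nearly all losses, Visits 1 and 2 essentially all preterm births, and Visit 3 most of them.
- A reader might call this immortal-time bias. Studying women still pregnant at a visit is a legitimate conditional (landmark) question; the immortal time is only the 96 h needed for inclusion.
- A reader might take the 96 h rule to require data at all five visits, which would remove every early event from every analysis. The wording permits that, but available cases per time point point the other way.
- A model with no events would be noticed and is unlikely to mislead by itself. The partly depleted sets and the mixed traces are the greater risk.

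**Conclusion.** The concern holds in a limited form. With sensors fitted within the stated weeks, the zeros follow from the calendar alone: no loss before 20 weeks at Visits 3 and 4, and no birth before 34 weeks at Visit 4. The 17, 3 and 0 days for birth before 37 weeks assume that the 96 h are accrued before delivery. The 33% to 90% loss of those births at Visit 4 also rests on the assumed timing of births. All of this matters for the analysis only if the time points are CGM visits. Separately, and on any reading, nothing stops postnatal glucose entering a Visit 4 profile.

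Two smaller points belong with it. Chronic hypertension is ordinarily present before the first sensor, so it is not an outcome of later CGM. Miscarriage is counted as drop-out in the sample size section but listed as an outcome elsewhere.

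This concerns a few secondary outcomes, mainly at late visits. Nothing here shows an effect on the primary outcomes' stated power. It should be corrected before analysis.

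**What to change.** In the statistical analysis plan section, or the full plan behind it:

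1. State whether the time point in the available-case sentence is the CGM visit.
2. Relate pregnancy loss before 20 weeks to Visit 1 only.
3. Relate birth before 34 weeks, birth before 37 weeks and gestational age at delivery to Visits 1–3, each among pregnancies ongoing once that visit's 96 h of CGM is complete.
4. Use Visit 4 for delivery timing only as a landmark or time-to-delivery analysis, starting from the end of the CGM data used.
5. Do not use Visit 5 CGM as an exposure for these outcomes.
6. Truncate each Visit 4 trace at the recorded delivery date, and apply the 96 h rule to what remains. The same cut can serve any earlier trace during which the pregnancy ends. Labour onset or admission would be a cleaner cut, but neither time is listed as collected.
7. Treat chronic hypertension as a baseline condition and keep new-onset hypertensive disorders as outcomes.
8. Reconcile miscarriage as drop-out with pregnancy loss as an outcome.

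The cost is wording and one data-cut rule. Gestational age at delivery is already recorded, so the cut at delivery needs no new data; a cut at labour onset or admission would. The downside is fewer outcome-by-visit estimates and slightly less Visit 4 data. No extra participants or visits are needed.
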